## Study interventions

### Resistance training with blood-flow restriction (BFR-RT)

Blood-flow restriction pressure will be determined before initiation of the training protocol. Participants will be asked to rest comfortably in supine position for approximately 10 min. A vascular Doppler probe (DV-600; Marted, Ribeirão Preto, São Paulo, Brazil) then will be placed over the tibial artery to capture its auscultatory pulse. A standard blood pressure cuff (175 × 94 mm, JPJ Industria Comercio Assistencia Técnica Mat Hospitalar Ltda Me, Sao Paulo, Brazil) will be attached to the participant’s quadriceps (near the inguinal fold region) and inflated to achieve auscultatory pulse interruption [24]. The restriction pressure used in the BFR-RT group will be determined as 50% of the pressure necessary for complete auscultatory pulse interruption in the resting condition [15].

The training protocol will consist of bilateral 1 × 30 repetitions and 3 × 15 repetitions at 20% 1-RM associated with blood flow restriction [15] in a knee extension machine (FISIOMAQ, Paraná, Brazil). The training session will start with a general warm-up on a cycloergometer (Ergo-Fit®, Pirmasens, Rheinland-Pfalz, Germany) at 20 km·h^− 1^ for 5 min. Next, the cuff (175 × 94 mm) will be placed proximally on the thigh (inguinal fold region) and inflated to 50% of complete blood flow restriction. The cuff will remain inflated throughout the exercise but will be released in the rest intervals. After the 6th training week, intensity will be increased to 30% 1-RM. A 2-min rest will be allowed between sets.

### Control group (CTRL)

The relaxation protocol will serve as a sham intervention in order to avoid possible effects from attention and contact time with the researchers [25]. The protocol will consist of 30-min sessions, including cephalocaudal muscle relaxation and breathing exercises.

## Assessments

### Primary outcomes

#### Maximal dynamic strength test (1-RM)

Maximal dynamic strength will be tested using one-repetition maximum tests (1-RM). Bilateral 1-RM tests will be performed on a knee extension machine, according to the protocol of Brown and Weir [26]. Initially, a warm-up of 5 min will be performed on a cycloergometer at 20 km·h^− 1^. Then, a specific warm-up for the assessed muscles will be performed using eight repetitions, followed by three repetitions at 50% and 70% of an estimated 1-RM, respectively. A rest interval of 2 min will be allowed between sets. Following warm-up, the 1-RM test will be initiated. Participants will perform both concentric and eccentric phases of the movement. An attempt will be considered successful if complete knee extension (~ 170°) is achieved. Up to five attempts will be allowed, with a rest interval of 3 min between attempts.

#### Muscle cross-sectional area (CSA)

Vastus lateralis (VL) muscle cross-sectional area (CSA) will be assessed using an ultrasound (US) machine. Procedures similar to Lixandrão et al. [27] will be adopted. Participants will be instructed to abstain from vigorous physical activities for at least 72 h. Following their arrival, participants will lay in a supine position for 15 min to allow fluid shifts to occur. Images will be collected using the US B-mode with a 7.5 MHz probe (Samsung, MySono U6, industria e comércio Ltda. São Paulo, Brazil). Surface gel will be applied to promote acoustic coupling while avoiding dermal deforming. The distance between the greater trochanter and the lateral epicondyle will be manually calculated, and the CSA will be obtained at the 50% point. Sequential markings will be made on participants’ skin to guide probe movement, and images will be acquired every 2 cm. Following data acquisition, VL CSA will be reconstructed according to Reeves et al. [28], whereby images will be sequentially opened and rotated using PowerPoint version 2007 (Microsoft, Redmond, WA, USA), until the full muscle area is visible. The CSA value will be assessed using the ImageJ polygonal tool. Each muscle area will be reconstructed two times, and the mean will be considered the true CSA value.

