### Pennation angle (PA)

VL PA will be assessed using B-mode ultrasound at the point corresponding to 50% of the femur’s length. The transducer will be placed longitudinally to muscle tissue and, when necessary, will be laterally tilted to better allow fascicle visualization [32]. Muscle fiber PA will be determined as the intersection of the fascicles with the deep aponeurosis, as assessed with ImageJ angular tool. Each image will be analyzed twice, and the mean value between both analyses will be considered as PA.

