### Fascicle length (FL)

B-mode ultrasound will be used for FL assessment at the same site used for PA, with the same probe placement. Linear extrapolation will be used to calculate FL whenever a fascicle extends itself beyond the ultrasound field of view [32]. FL will be calculated two times per image. The mean value will be used as true FL.

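### The article sets out hand reading of vastus lateralis CSA, a primary outcome, but states no masking of the reader, leaving the 12- and 24-week readings open to bias by arm

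*Protocol article*

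**What the plan says.** The Primary outcomes section lists two measures, 1-RM and CSA. For the second, "Vastus lateralis (VL) muscle cross-sectional area (CSA) will be assessed using an ultrasound (US) machine". The reading takes place on stored images after acquisition. First, "images will be sequentially opened and rotated using PowerPoint version 2007 (Microsoft, Redmond, WA, USA), until the full muscle area is visible". Then "The CSA value will be assessed using the ImageJ polygonal tool". The only safeguard described is repetition: "Each muscle area will be reconstructed two times, and the mean will be considered the true CSA value".

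Two secondary outcomes are also measured by hand on ultrasound images. Pennation angle is the fascicle–aponeurosis intersection "as assessed with ImageJ angular tool". For fascicle length, "Linear extrapolation will be used to calculate FL whenever a fascicle extends itself beyond the ultrasound field of view". Both are averages of two analyses.

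No section mentions masking of participants, assessors, image readers or analysts. The control intervention is justified on other grounds: "The relaxation protocol will serve as a sham intervention in order to avoid possible effects from attention and contact time with the researchers". The Berger-Exner test in the Randomization section looks for selection bias at allocation, not for bias in measurement. The Background states the expected direction, which is that muscle mass will rise with BFR-RT.

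**The concern.** Deciding when the whole muscle is in view, how the frames fit together and where the border runs are judgements. A reader who knows that an image is a 12-week scan from a trained participant, and who shares the stated hypothesis, can place borders slightly further out without intending to. The result would look like hypertrophy, and nothing in the trial data could tell the two apart.

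This matters more here than in many trials. Participants know whether they are doing cuffed knee extension or relaxation, and 1-RM depends partly on effort, although it has a defined success criterion and a limit on attempts. CSA reading is the part of the primary assessment that can readily be masked, because it is done offline on stored images.

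**Working it through.** There is no figure in the plan to reproduce. It gives a target of 30 participants but no alpha, power, effect size or SD. The check has three parts.

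**1. Which readings can knowledge of arm affect?** The Randomization section groups participants into quartiles by initial 1-RM and CSA before assigning arms, and the Fig. 2 legend places the baseline ultrasound before allocation. Baseline CSA is therefore read when no arm exists. The 12- and 24-week images are acquired after allocation.

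Let b0 be the mean reading error at baseline, which is the same in both arms in expectation. Let bT and bC be the mean reading errors at a later visit in the BFR-RT and control arms. The bias in the between-arm difference in change is

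(bT − b0) − (bC − b0) = bT − bC.

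The baseline error cancels, and the arm-related error at follow-up passes through in full. An error tied only to visit (bT = bC ≠ b0) cancels between arms. It does enter the within-group effect sizes for 0–12 and 0–24 weeks that the Data analysis section plans to report.

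**2. Does averaging two reconstructions help?** If each reading has random error variance s² and a shared directional error b, the mean of two independent readings has error variance s²/2 and bias (b + b)/2 = b. Precision improves and the bias is unchanged.

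**3. How sensitive is the conclusion?** Assumed inputs:
- 15 per arm (the article gives 30 in two groups and no ratio)
- a two-sided 5% level
- an unpaired t-test on change with 28 degrees of freedom
- no true effect
- a pure reading bias of d SDs of change

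The noncentrality is d / √(2/15) = d / 0.365. The false-positive rate is the probability that the noncentral t exceeds the 5% critical value in either direction.

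| Bias d (SD of change, assumed) | Noncentrality | Rejection, both tails | Rejection favouring BFR-RT |
|---|---|---|---|
| 0 | 0 | 5.0% | 2.5% |
| 0.1 | 0.27 | 5.8% | 4.5% |
| 0.2 | 0.55 | 8.3% | 7.6% |
| 0.3 | 0.82 | 12.5% | 12.2% |
| 0.5 | 1.37 | 26.2% | 26.2% |

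A normal approximation for the BFR-RT tail gives 4.6%, 7.9%, 12.8% and 27.7% for biases of 0.1, 0.2, 0.3 and 0.5 SD, close to the last column.

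**The case against.** The strongest reply is that silence is not evidence. This is a journal article that condenses a fuller protocol. It points to a SPIRIT checklist in an additional file, and the CSA section relies on two cited method papers, none of which is at hand. Readers may already be masked. This stands in part: the documents do not support a claim that the readers are unmasked, only that masking is not stated. It does not remove the point. The CSA section goes down to probe frequency, software version and number of reconstructions, so a masking step would be expected there, and a team following the text would have no instruction to code files.

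A second reply is that the timing of allocation already protects part of the data. This is correct. A reader might infer that CSA at all three visits is exposed to knowledge of arm, but baseline CSA is not. The same timing rules out the simplest remedy, which is to hold all reading until after week 24, because allocation needs the baseline values.

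Third, a reader might take fascicle length to be extrapolated by eye. The article says only that linear extrapolation is used, which is a calculation. The exposure there is in the manual measurement.

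Finally, the error rates come from a simple t-test. The plan is a mixed model over three visits, with Hommel-adjusted and unadjusted p values both reported. This also stands, so the table shows sensitivity and is not the trial's own error rate.

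**Conclusion.** The point holds as follows. The article prescribes a judgement-dependent reading of a primary outcome and states no masking of the reader. Any arm-related error in the 12- and 24-week readings goes undiminished into the between-arm change, and the stated safeguard of averaging does not address it. The same applies to the manual pennation angle and fascicle length readings.

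The size of any such error cannot be derived from the documents. Under the assumptions listed, 0.1 SD would do little (5.8%), 0.3 SD would raise the false-positive rate to about 12%, and 0.5 SD to about 26%. A reader might infer that the trial is biased, or that its false-positive rate is 12%. The documents support neither. They show an unprotected step that can be protected cheaply, so the change is worth making, though nothing here shows that the trial is invalid.

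**What to change.** Add to the CSA, pennation angle and fascicle length sections:

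- Baseline CSA is read before allocation as now, and that reading is used only for forming the quartiles.
- For the analysis, all images are stored under random codes with name, arm, date and visit removed.
- After the 24-week visit, an existing team member without the code list reads the 0-week (a re-read), 12-week and 24-week images in random order in one batch.
- These masked values are used for the analysis of CSA, pennation angle and fascicle length. The code list is opened only after the values are locked.

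The cost is file coding, one repeat reading of the baseline images and later availability of the 12-week values. No extra participant, visit or scan is needed. Recruitment was still open at submission, and images already collected can be coded and read in the same way. Coding protects the reading but not the acquisition of the images. If masked reading is already in place, one sentence in each of the three sections is enough.

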### Secondary outcomes

#### Child-Pugh class and MELD score

Participant blood samples will be collected and analyzed in a professional clinical laboratory. To classify these samples according to Child-Pugh class and Meld score at 0 W, 12 W and 24 W, they will be screened for aspartate aminotransferase, alanine aminotransferase, creatinine, albumin, and bilirubin. Additionally, clinical screenings will be carried out by a medical professional at the same time points for physical assessment of the participants.

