In this sense, evidence shows that low-load RT combined with partial blood flow restriction (BFR-RT) results in significant muscle mass gains, comparable to high-load RT [15, 16] or low-load RT to muscle failure [17]. Its applicability in frail populations (e.g., elderly and cardiac patients) also has been verified, with positive outcomes after the intervention period [15, 18, 19], including functional performance [20]. Additionally, BFR-RT has been found to result in significantly smaller increases in systolic blood pressure, diastolic blood pressure and heart rate than both low-load RT and high-load RT performed to failure [21]. Thus, BFR-RT could prove to be a safe RT method in LC patients, improving muscle strength and mass while avoiding marked increases in blood pressure and, possibly, in portal pressure and variceal bleeding.

Thus, this study aims to investigate the effects of BFR-RT on muscle strength, muscle mass, fiber Pennation angle, fascicle length, functional performance, and risk of falls in LC patients. Additionally, we aim to verify whether BFR-RT is a safe method for this population. Our hypothesis is that BFR-RT will promote increases in muscle strength, muscle mass, and functional performance, while reducing the risk of falls, with no aggravation in LC condition.

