**Fig. 2 Fig2:**
[figure not shown]
Design overview. Before the training period (0 W), all participants will be screened for Child-Pugh class and MELD score, as well as for quality of life, functional capacity, and risk of falls Participants will also be requested to provide a dietary record for caloric intake calculation. At least 48 h later, participants will perform a 1-RM test. Then 72 h later, vastus lateralis muscle CSA, PA, and FL will be assessed. Participants will then be randomly allocated between a training (resistance training with blood-flow restriction - BFR-RT) and control (CTRL) group. After 12 weeks of intervention (12 W), all of the previous parameters will be reassessed. A no-intervention period of 12 weeks will be carried out and, at follow-up (24 W), participants will be reassessed in order to verify the interventions carryover effects

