### Eligibility criteria

Eligibility criteria are 1) liver cirrhosis diagnosed by histopathological evaluation, hepatic elastography, or by clinic, radiologic or endoscopic criteria and 2) age ≥ 18 and ≤ 70 years. Exclusion criteria are 1) less than 6 months of alcohol abstinence, 2) MELD score > 15, 3) Child-Pugh class C, 4) decompensated chronic diseases, 5) diabetes mellitus, 6) hepatocellular carcinoma or others neoplasia, 7) previous liver transplant, 8) severe ascites, 9) persistent hepatic encephalopathy, 10) coagulation disorders characterized as INR ≥ 1.5 or platelets ≤ 75.000, or 11) medical contraindications for physical exercise practice.

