## Data analysis

Following visual inspection, data normality will be assessed using the Shapiro-Wilk test. In case of normal distribution, a one-way repeated measures analysis of variance (ANOVA) will be implemented to test for differences in baseline values. Then, a mixed model will be applied for each dependent variable (Child-Pugh class, MELD score, SF-36 and FSS scores, dietary records, TUG, 6MWT, SRT, 1-RM, CSA, PA and FL), having group (BFR-RT and CTRL) and time (0 W, 12 W and 24 W) as fixed factors, and participants as random factors. In case of non-normal data distribution, a Kruskal–Wallis test will be implemented to test for differences in baseline values. Then, the Friedman test will be used to analyze repeated measures. To avoid multiplicity interference on data analysis, adjusted *p* values will be calculated for all variables. Adjusted *p* values will be calculated using Hommel’s procedure, and both adjusted and non-adjusted values will be reported. Additionally, within-group (0-12 W and 0-24 W changes) and between-group effect sizes will be calculated using Cohen’s *d* [33] for each outcome. Finally, the minimal clinically important difference will be analyzed with distribution-based methods [34]. Statistical analysis will be carried out using SAS 9.3 software (SAS institute Inc., Cary, NC).

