## Discussion

LC was reported as the 14th most common cause of death worldwide in 2012, resulting in 1.03 million deaths per year [35], with sarcopenia affecting up to 70% of the patients afflicted by LC [3]. If proven efficient in countering sarcopenia onset or reducing sarcopenia progression, new therapeutic options (e.g., BFR-RT) could help reduce the treatment costs of patients with LC.

As such, the present study aims to verify whether BFR-RT will result in important improvements in muscle strength and mass in patients with liver cirrhosis, as well as verifying any significant differences in functional performance and risk of falls. In addition, the LC Child-Pugh class and MELD score will be evaluated in order to determine BFR-RT safety and effects on the disease’s symptoms. To our knowledge, this will be the first intervention study to investigate BFR-RT in this population. Considering that current evidence shows BFR-RT is a safe method, even for frail populations [15, 17, 18], we believe BFR-RT will result in important increases in muscle mass and strength, accompanied by increases in functionality, with no negative outcomes on cirrhosis condition. There are some limitations to this study. The limited follow-up period prevents us from drawing conclusions about the long-term effects of the proposed intervention. Second, we opted to limit our sample to patients without severe LC complications (i.e., Child-Pugh class B and C and MELD > 15), limiting our ability to generalize our results to patients with decompensated LC.

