## Trial status

This is version 1 of this protocol, written on July 13, 2018. Participant recruitment began in September 2018. Recruitment was expected to be completed on October 2018; however, an insufficient number of participants were recruited. Thus, recruitment is expected to be completed in July 2020. Recruitment was ongoing at the time of submission.

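### The blood tests listed for scoring Child-Pugh and MELD omit INR, so as written MELD cannot be computed at 12 and 24 weeks; Child-Pugh is also modelled as class rather than points

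*Protocol article*

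**What the plan says.** In the protocol article, the Secondary outcomes section on Child-Pugh class and MELD score gives one purpose for the blood samples, which is to score both indices at 0, 12 and 24 weeks. It then names the tests: "they will be screened for aspartate aminotransferase, alanine aminotransferase, creatinine, albumin, and bilirubin". The same paragraph adds a clinical screening by a medical professional at each of these visits.

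INR appears as a measurement only under Eligibility criteria, where one exclusion is "coagulation disorders characterized as INR ≥ 1.5 or platelets ≤ 75.000". MELD above 15 and Child-Pugh class C are also exclusions there. The legend to Fig. 2 lists Child-Pugh class and MELD among the baseline assessments and says: "After 12 weeks of intervention (12 W), all of the previous parameters will be reassessed". INR is not named among those assessments.

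Under Data analysis, "a mixed model will be applied for each dependent variable (Child-Pugh class, MELD score, SF-36 and FSS scores" and the remaining outcomes). The article does not mention Child-Pugh points. The Discussion says that "the LC Child-Pugh class and MELD score will be evaluated in order to determine BFR-RT safety", and the hypothesis in the Background ends "while reducing the risk of falls, with no aggravation in LC condition".

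**The concern.** The list of tests does not match the purpose given for it. It leaves out a laboratory value that both scores require and includes two enzymes that neither score uses. This goes beyond detail left to a fuller document: the article names the tests and says what they are for, and the named set is not sufficient.

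What is at stake is part of the safety conclusion. The two scores are the stated means of checking that training does not worsen the liver disease. If the list were followed to the letter, the finer score, MELD, could not be produced after training starts. Child-Pugh would lack one item, and what remained of it would be analysed as a class with few levels.

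**Working it through.** The article gives no figure to reproduce on this point. The check sets the listed tests against the inputs of each score. The score definitions below are the standard ones and are assumed, since the article does not print them.

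| Input | MELD | Child-Pugh | Source at 12 and 24 weeks |
|---|---|---|---|
| Bilirubin | yes | yes | listed |
| Creatinine | yes | no | listed |
| Albumin | no | yes | listed |
| INR (or prothrombin time for Child-Pugh) | yes | yes | not listed |
| Ascites, encephalopathy | no | yes | clinical screening can supply them |
| AST, ALT | no | no | listed |

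One of three laboratory inputs is missing for each score, and two of the five listed tests enter neither.

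**Visits affected.** The target is 30 participants (Design overview), each with two follow-up visits: 30 × 2 = 60 visits without a listed INR, before any dropout. A value should exist at entry because eligibility depends on it.

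**Size for MELD.** Assume the classic INR term, 11.2 × ln(INR), set to zero at INR 1 or below.

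- INR 1.0: 0 points
- INR 1.2: 11.2 × ln(1.2) = 2.0
- INR 1.4: 11.2 × ln(1.4) = 3.8
- INR 1.49, just under the exclusion limit: 11.2 × ln(1.49) = 4.5
- If INR rises after entry: 5.9 at 1.7 and 7.8 at 2.0

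Across the eligible INR range the unlisted term is therefore worth 0 to about 4.5 points, against an entry cap of MELD 15.

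**Size for Child-Pugh.** Assume that the INR item stays at its minimum until about 1.7. Entry requires INR below 1.5, so every eligible participant starts at the minimum on this item. It changes only if INR later reaches about 1.7. The total is formally incomplete without INR, but the missing item would rarely alter it.

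**Class against points.** Assume the usual bands: A 5–6, B 7–9, C 10–15. With class C excluded, entry totals run from 5 to 9. A one-point worsening gives 5→6 (A to A), 6→7 (A to B), 7→8 and 8→9 (B to B), and 9→10 (B to C). Class changes from 2 of the 5 possible totals. This counts totals, not patients, because the article gives no distribution of entry totals. The Discussion's limitation sentence, with "Child-Pugh class B and C and MELD > 15", reads as if class B were outside the sample too. On that reading all participants start in A, class is constant at baseline, and a move from 5 to 6 is never seen.

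**The case against.** The strongest reply is that the sentence is merely incomplete. It does not say that only these tests will be run. The investigators must already obtain INR to apply the INR and MELD exclusions, and they commit to scoring MELD again at 12 and 24 weeks. They may well measure INR in practice. This stands as a limit on the consequence: the article does not show that the scores will go uncomputed. It does not rescue the list, which is stated for scoring and is insufficient for it.

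A reader might infer that the entry INR will be carried forward, so that later deterioration is hidden in favour of the hypothesis. Nothing in the article proposes this. A reader might also count 120 affected scores, but that counts the same 60 INR results once for each score. Nor does the gap leave the trial without safety evidence: adverse events are a separate aim, and clinical screening takes place at each visit. Measuring AST and ALT does no harm; only their description as score inputs is wrong.

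On class against points, it can be said that class is the outcome the article names throughout and that MELD, a finer scale, is analysed beside it. The first part stands as a cost, because moving to points alters how a named secondary outcome is analysed after recruitment has begun. The second part is weaker, since MELD is the score that the listed tests cannot produce.

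**Conclusion.** The concern holds as a minor one. The tests named for scoring Child-Pugh and MELD omit INR or prothrombin time. If the list is followed, up to 60 follow-up visits lack that input, so MELD cannot be computed and Child-Pugh is incomplete. The practical effect falls mainly on MELD. Analysing Child-Pugh as class adds a second, smaller loss, since worsening within a class cannot show.

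Both scores are secondary outcomes used to judge safety. The primary outcomes, 1-RM and vastus lateralis CSA, are not touched. The conclusion rests on the standard score definitions. The 11.2 weight, the 1.7 cut-off and the class bands are assumed and serve only to show size.

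**What to change.** In the Secondary outcomes section, the text could read:

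> At 0, 12 and 24 weeks, blood will be tested for bilirubin, creatinine, albumin and INR. Ascites and encephalopathy will be graded at the clinical screening of that visit. MELD, Child-Pugh points and Child-Pugh class will be calculated from values of the same visit. Where no same-visit INR exists, the scores for that visit will be treated as missing, and the number missing will be reported by arm. AST and ALT are safety laboratory tests and are not score inputs.

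Under Data analysis, make Child-Pugh points the dependent variable in the mixed model and show shifts in class by arm descriptively.

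The cost is up to 60 extra INR assays (30 × 2) at draws already planned, provided the eligibility INR can serve as the 0-week value, plus a dated amendment to how a secondary outcome is analysed. If INR is already measured, the first change is only a correction of wording. There are two downsides. The article states that "Participant recruitment began in September 2018", so some follow-up visits may already have been held without INR, and their scores may stay missing. Points also move only when a component crosses a band, so smaller laboratory changes would still not show in the total.
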